### Sample size calculation

We anticipate that the intervention will reduce the days of absence among primary caregivers by 50% to 2/24 (8.3%), assuming a rate of absence from work of 17% (4/24) days in a month (unpublished data). A total sample size of 338 (rounded to 340) would be needed to estimate a 50% reduction in the prevalence of absence from work with 80% power, at a 5% significance level, 10% attrition rate, and a design effect of 1.5. We will therefore have approximately 170 primary caregivers in each arm.

The minimum total required sample size for detecting a difference for a two-arm evaluation can be computed as:$$n = \frac{{\left[ {\left( {Z_{1 - \frac{\alpha }{2}}\sqrt {2\underline {pq} } } \right) + Z_{1 - \beta }\sqrt {\left( {P_1\left( {1 - P_1} \right) + P_2\left( {1 - P_2} \right)} \right)} } \right]^2}}{{\left( {P_1 - P_2} \right)^2}}$$where$$\underline p = \frac{{\left( {P_1 + P_2} \right)}}{2}\,{{{\mathrm{and}}}}\,\underline q = 1 - \underline p$$*P*_1_ is the observed proportion of absence and *P*_2_ is the expected proportion of absence after the intervention.

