### Data analysis

Thematic analysis will be used to systematically analyze all qualitative data (in line with the key questions) through five stages: familiarization, defining themes, coding, charting, and interpretation. During the familiarization stage, all transcripts will be read in-depth. We will generate codes by interrogating the data and linking narrative content. In the final stages, we will categorize the codes to identify overarching themes. Members of the research team will then meet to jointly deliberate on the themes in order to develop a codebook that they will use to carry out the thematic analysis independently. The transcripts will be coded using NVivo.

A micro-costing approach will be followed and intervention costs will be derived by entering and analyzing data into a customized costing tool created in MS Excel. Cost data will be entered regularly into the tool, accounting for different timings for cost occurrence. Costs will be allocated to the following categories: personnel, materials, infrastructure, capital, supervision, monitoring and mentoring, airtime, transportation, and joint costs. Capital and investment costs will be annualized over their expected useful life. In addition, donated goods or volunteer time will be appropriately accounted for from an economic perspective. Costing data will be summarized and described for each cost category by the target population (mamapreneurs or caregivers). We will use a single summative worksheet to determine the total cost data for each target population. This will be combined with effect data to estimate the incremental cost-effectiveness of the program. Sensitivity analyses will be conducted on the estimates.

Quantitative data will be cleaned and analyzed using STATA version 16. We will use the difference-in-differences (DID) estimator to compare changes in outcomes (such as labor participation) over time between the intervention and comparison groups to estimate impact. The DID gives a stronger impact estimate than a single difference, which only compares the difference in outcomes between treatment and comparison groups following the intervention. Applying the DID method removes the difference in the outcome between treatment and comparison groups at the baseline.

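### The sample size treats a share of days as a share of women and powers an after-only contrast, so the 80% power claimed for 340 is not derived for days of absence or for the planned difference-in-differences estimator

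*Protocol article*

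**What the plan says.** All of the sample size reasoning is in the protocol article, Methods, Sample size calculation.

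- The starting value is a share of working days: "assuming a rate of absence from work of 17% (4/24) days in a month (unpublished data").
- The effect is also in days. The intervention is expected to "reduce the days of absence among primary caregivers by 50% to 2/24 (8.3"%).
- The next sentence gives the target another name, the number "needed to estimate a 50% reduction in the prevalence of absence from work".
- The design inputs are "with 80% power, at a 5% significance level, 10% attrition rate, and a design effect of 1.5".
- The result is "A total sample size of 338 (rounded to 340) would be needed", and then "We will therefore have approximately 170 primary caregivers in each arm".

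The printed formula is the usual one for two independent proportions, with a pooled term and an unpooled term. Its second proportion "is the expected proportion of absence after the intervention". It has no baseline term and no within-woman correlation.

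The Data management section plans surveys at baseline, 6 months and 12 months. Under Data analysis the estimator is named: "We will use the difference-in-differences (DID) estimator to compare changes in outcomes (such as labor participation) over time between the intervention and comparison groups".

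**The concern.** Two things do not match.

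**Unit.** 4/24 and 2/24 are mean days absent divided by 24. The formula reads them as the fraction of women with a yes/no event and gives each woman variance P(1−P). For a share of 24 days, that variance is right only if every woman misses all 24 days or none. What matters for days is the between-woman SD, and the article gives none.

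**Estimator.** The formula describes one comparison after the intervention. DID compares changes, so its variance depends on the correlation between a woman's baseline and later values. The calculation does not use that correlation.

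At stake is how a null result will be read. This paragraph is the only justification for 170 per arm. If its 80% is not the power of the planned analysis, a reader cannot tell an ineffective programme from an imprecise estimate.

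**Working it through.** **Inputs from the article.** P1 = 4/24 = 0.1667, P2 = 2/24 = 0.0833, two-sided 5% (z = 1.96), 80% power (z = 0.8416), design effect 1.5, attrition 10%, 170 per arm. The difference is 2 days.

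**Assumed, because the article does not give them.** SD of days absent 3 to 6, the same in both arms and at both times; baseline-endline correlation ρ from 0.2 to 0.6.

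**Step 1: the plan's own figure.** Mean proportion 0.125.
- Pooled term: √(2 × 0.125 × 0.875) = 0.4677.
- Unpooled term: √(0.1389 + 0.0764) = 0.4640.
- n = (1.96 × 0.4677 + 0.8416 × 0.4640)² / 0.0833² = 1.7087 / 0.006944 = 246.06.

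This formula returns the number per arm, although the article labels it a total. Inflated, 246.06 × 1.5 / 0.9 = 410 per arm, about 820 in total. With the rounded rates 0.17 and 0.083 it is 228 per arm, 380 after inflation, 760 in total. Reading the output as a total gives 410 or 380. None of these is 338. The closest simple route found is 228 × 1.5 = 342, which calls a per-arm number a total and leaves out attrition.

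**Step 2: power of the plan's own contrast at 170 per arm.** Effective number per arm: 170 × 0.9 / 1.5 = 102. Power = Φ[(0.0833 × √102 − 1.96 × 0.4677) / 0.4640] = Φ(−0.16) = about 44% (46% with 0.17 and 0.083).

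**Step 3: what the unit error does alone.** For a quantity between 0 and 24 with mean 24P, the SD cannot exceed 24√(P(1−P)). That is 8.94 days at P1 and 6.63 days at P2. If days were independent within a woman, the SD at P1 would be √(24 × 0.1667 × 0.8333) = 1.83 days. The formula therefore uses the ceiling. For an after-only comparison of mean days, n per arm = 2 × (1.96 + 0.8416)² × SD² / 2², then × 1.5 / 0.9:

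| SD (days) | n per arm | after inflation |
|---|---|---|
| 3 | 35.3 | 59 |
| 4 | 62.8 | 105 |
| 5 | 98.1 | 164 |
| 6 | 141.3 | 235 |

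All are below the 410 that the binary formula gives.

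**Step 4: adding DID.** With equal variances and two waves, the variance is multiplied by 2(1−ρ), which is above 1 for ρ below 0.5 and below 1 above it. Power at 102 effective per arm = Φ[2 / (SD × √(2(1−ρ)) × √(2/102)) − 1.96]:

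| SD (days) | ρ = 0.2 | ρ = 0.4 | ρ = 0.6 |
|---|---|---|---|
| 3 | 96% | 99% | >99% |
| 4 | 81% | 90% | 98% |
| 5 | 62% | 74% | 89% |
| 6 | 47% | 58% | 76% |

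The inflated requirement over this grid runs from 58.9 × 0.8 = 47 to 235.5 × 1.6 = 377 per arm, on either side of 170.

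**Step 5: keeping the yes/no scale under DID.** The variances differ once the rate has fallen, so the break-even moves to ρ of about 0.57. The ratio of DID to after-only variance is 1.62 at ρ = 0.3, 1.17 at 0.5 and 0.94 at 0.6. Power at 170 per arm with ρ = 0.3 is about 30%.

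**The case against.** The strongest reply is that no harm is shown. Binary variance is the maximum for a day share, so the unit error by itself is on the safe side. Powering on an after-only contrast is a common simplification, and it is conservative when ρ exceeds 0.5. Both statements are correct. They do not rescue 340, because 340 is well short of what the binary formula itself returns (Steps 1 and 2).

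A second reply is that the article does not say how absence is recorded. Absence is not in its list of impact measures, and the analysis section never names it as a DID outcome; the examples there are labor participation and a proportion of women empowered. That stands. A day count per woman is inferred from the way the effect is described. A yes/no item would justify binary variance, but the mismatch with DID would remain.

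A third reply is that there are three survey waves. If the 6- and 12-month values were averaged, with equal correlations (an assumption), the factor would be 1.5(1−ρ). Power at SD 5 and ρ = 0.4 would then be 85%, not 74%. This also stands, and it is a reason to state which waves are used. The exact DID model may be left to an analysis plan; the basis of a power figure that the article prints is a different matter.

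A reader might infer from the mixed units that the trial is too small for days of absence. The documents do not support that: with an SD of 4 days or less, 170 per arm has at least about 80% power over the whole assumed range of ρ.

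**Conclusion.** The point holds as a fault in how the sample size is justified. Shares of days are used as shares of women, and an after-only contrast is powered where DID is planned, so the stated 80% is not the power for the outcome described or for the planned estimator.

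The net direction is unknown. The 47% to over 99% range rests on an assumed SD of 3 to 6 days, an assumed ρ of 0.2 to 0.6, equal SDs throughout and two waves. An SD of 7 is left out because a mean of 2 days in 24 allows at most 6.63.

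What needs no outside assumption is that the stated inputs lead to about 820 women in total, and that 170 per arm gives about 44% power for the article's own contrast. The paragraph should be corrected. The finding does not show that the trial is underpowered for days of absence, and it does not bear on bias in the effect estimate.

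**What to change.** Keep 170 per arm; the abstract reports both groups as already recruited and in follow-up. Rewrite the sample size paragraph as follows:

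1. State the effect as a difference in mean days absent, 4 versus 2 of 24.
2. Give the between-woman SD and its source: the unpublished data behind 4/24 if they hold it, otherwise the trial's own baseline survey.
3. State ρ with a range, and say whether two or three waves enter the estimator.
4. Apply the design effect and attrition, and report the resulting power at 170 per arm.
5. Correct the formula's label from total to per arm, and explain or withdraw 338.
6. If absence is analysed, analyse it as days per woman.

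The cost is one recalculation and one rewritten paragraph. Recruitment and data collection do not change, provided that absence is recorded as days.

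### The sample size formula gives a number per arm but is labelled and used as a total, so 170 per arm has about 44% power on the plan's own inputs, not 80%.

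*Protocol article*

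**What the plan says.** All of this is in the Protocol article, Methods, Sample size calculation.

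- **Control rate:** "assuming a rate of absence from work of 17% (4/24) days in a month".
- **Target:** the intervention is expected to "reduce the days of absence among primary caregivers by 50% to 2/24 (8.3"%).
- **Operating characteristics:** "with 80% power, at a 5% significance level, 10% attrition rate, and a design effect of 1.5".
- **Result:** "A total sample size of 338 (rounded to 340) would be needed to estimate a 50% reduction in the prevalence of absence from work".
- **Allocation:** "We will therefore have approximately 170 primary caregivers in each arm".
- **Formula:** it is introduced with "The minimum total required sample size for detecting a difference for a two-arm evaluation can be computed as". The expression has the root of 2p̄q̄ multiplied by Z(1−α/2), plus the root of P1(1−P1)+P2(1−P2) multiplied by Z(1−β), all squared and divided by (P1−P2)².

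The abstract reports 170 recruited to each group.

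**The concern.** Both variance terms in the printed expression belong to a difference between two independent groups of n each. The n it returns is therefore the size of one group, and the total for two equal arms is 2n. The article calls n the total and then halves the stated figure to reach 170 per arm.

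This is the article's only power statement. A reader of a null result on absence would take it as coming from a study with an 80% chance of detecting a halving. If the true chance on the same assumptions is below one half, that reading is unsafe, and the study is meant to inform scale-up and childcare policy.

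**Working it through.** **Inputs, all from Sample size calculation.** P1 = 4/24 = 0.1667 (printed as 17%); P2 = 2/24 = 0.0833 (printed as 8.3%); two-sided α = 0.05, since the formula uses Z(1−α/2), so Z = 1.960; power 80%, so Z = 0.8416; design effect 1.5; attrition 10%; 170 recruited per arm.

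**1. Trying to reproduce 338.** The printed formula with the exact fractions has p̄ = 0.125 and q̄ = 0.875:

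- first term: 1.960 × √(2 × 0.125 × 0.875) = 0.9167
- second term: 0.8416 × √(0.1389 + 0.0764) = 0.3905
- n = (0.9167 + 0.3905)² / 0.08333² = 246.1

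| Inputs | n per arm | × 1.5 | / 0.9 | Two arms |
|---|---|---|---|---|
| 4/24 vs 2/24 | 246.1 | 369.1 | 410.1 | about 820 |
| 0.17 vs 0.083 | 228.0 | 342.0 | 380.0 | about 760 |

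Rounding up at each step moves 820 to 824. Applying attrition as × 1.1 instead of / 0.9 gives 406 or 376 per arm. The stated total of 338 is not reproduced.

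**2. Taking the label at face value.** If n were a total, the same inputs would give 376 to 410, still not 338. The paragraph disagrees with itself under either reading.

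**3. Where 338 may come from.** With 0.17 and 0.083, the unpooled form of the formula gives 225.2 per arm, and 225.2 × 1.5 = 337.9. That is a per-arm number with the design effect but without attrition. This is a conjecture, and nothing below depends on it.

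**4. Power with 170 per arm.** Effective n per arm is m = 170 × 0.9 / 1.5 = 102. Inverting the printed formula:

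Power = Φ{ [ |P1−P2|·√m − 1.960·√(2p̄q̄) ] / √(P1(1−P1)+P2(1−P2)) }

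With the exact fractions: (0.08333 × √102 − 0.9167) / 0.4640 = (0.8416 − 0.9167) / 0.4640 = −0.162, and Φ(−0.162) = 0.436.

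| Allowance made | Effective n per arm | Power, 4/24 vs 2/24 | Power, 0.17 vs 0.083 |
|---|---|---|---|
| Design effect and attrition (as stated) | 102 | 43.6% | 46.3% |
| Design effect only | 113.3 | 47.5% | 50.4% |
| Attrition only | 153 | 59.7% | 63.0% |
| Neither | 170 | 64.3% | 67.6% |

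No row reaches 80%. Even 340 in each arm (effective 340 × 0.9 / 1.5 = 204) would give 72% to 75%, so the stated attrition also appears to have been left out.

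**5. Detectable effect.** With 102 effective per arm and P1 = 4/24, 80% power requires P2 = 0.046. That is a relative reduction of 1 − 0.046/0.1667 = 72%, against the 50% assumed.

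**The case against.** The strongest objection is that 44% is not the study's real power. The quantity in the article is a share of days: 4 of 24 falling to 2 of 24. Entering it as a proportion of women assumes in effect that each woman is absent on every day or on none, which is the largest variance these means allow (SDs of about 8.9 and 6.6 days). The article gives no SD for days absent. Over an assumed range, a plain two-sample comparison of a 2-day difference with 102 effective per arm has power of about 95% at SD 4, 82% at SD 5, 66% at SD 6 and 53% at SD 7, and it reaches 80% up to an SD of about 5.1 days. The planned difference-in-differences analysis also uses baseline data, so its precision depends on a within-woman correlation that the article does not give, and realised power could be higher or lower than 44%.

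This stands as a caution on interpretation: 44% to 46% is conditional on the binary framing and does not forecast how the study will turn out. It does not rescue the stated figure. The article sizes the study by comparing two proportions and claims neither a continuous scale nor a gain from baseline data. On the calculation it prints, 338 in total does not give 80% power.

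The origin of 338 is also uncertain. Other routes come close, such as a one-sided continuity-corrected number per arm (336), but they contradict the printed formula. The error is established without knowing the route.

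Finally, this is not a matter of detail left to a fuller document: the formula, inputs, result and allocation are all printed, and they do not agree.

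**Conclusion.** The concern holds. The formula is per arm, is labelled a total, and the stated total is split into 170 per arm. On the plan's own inputs the requirement is about 380 to 410 per arm (760 to 820 in total). The 170 per arm gives 44% power with the exact fractions or 46% with the rounded percentages. No combination of the stated allowances lifts power above 68%. On those inputs the study is more likely to miss the assumed halving than to detect it.

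This rests on the stated two-sided 5% level, on the design effect and attrition as printed, and on the article's treatment of absence as a binary outcome per woman. The size of the shortfall would change on another outcome scale. The mislabelled formula and the unsupported 80% would not.

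**What to change.** - In Sample size calculation, describe the formula's result as the number required per arm, not the total.
- Withdraw the statement that 338 (340) in total gives 80% power.
- State what 170 per arm delivers on the printed inputs, with both allowances applied: about 44% power for a 50% reduction, or 80% power for a reduction of about 72%. Mark these figures as conditional on treating absence as yes/no per woman.
- Recompute power on the scale that will be analysed. If that is days absent per woman, give the assumed SD and its source, and state any assumed baseline correlation. Once that figure is available, it should stand as the study's power in place of the binary one.

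The cost is one rewritten paragraph and a less favourable power statement on the present inputs. Recruitment is reported as done at 170 per arm, and no further participants are asked for.

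### The stated sample size of 338 omits the 10% attrition it claims to include, and it is a per-arm result used as a total, so power at 170 per arm is about 50% before any loss

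*Protocol article*

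**What the plan says.** All of the relevant text is in the protocol article, Methods, Sample size calculation. The rates are set by "assuming a rate of absence from work of 17% (4/24) days in a month" and an anticipated halving to 2/24, printed as 8.3%. The result is given as "A total sample size of 338 (rounded to 340) would be needed to estimate a 50% reduction in the prevalence of absence from work", and the same sentence lists what the number carries: "with 80% power, at a 5% significance level, 10% attrition rate, and a design effect of 1.5". The section continues: "We will therefore have approximately 170 primary caregivers in each arm".

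It then prints a two-proportion formula with Z at 1 − α/2, a pooled variance under the null and no continuity correction. It introduces the formula with "The minimum total required sample size for detecting a difference for a two-arm evaluation can be computed as".

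**The concern.** Attrition is named as an input to 338, so a reader will take it that 10% of the women can be lost without harm to the stated power. If 338 is already used up by the formula and the design effect, that allowance does not exist. It matters because both arms are followed for a year, with surveys at baseline, 6 and 12 months, and the plan itself expects some loss.

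The same check raises a second matter, which decides how large the consequence is: whether the formula's result is the number for both arms together or for each arm.

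**Working it through.** **Inputs** (all from the sample size section): P1 = 0.17 (or 4/24 = 0.1667); P2 = 0.083 (or 2/24 = 0.0833); two-sided α = 0.05, so Z = 1.960; power 80%, so Z = 0.8416; design effect 1.5; attrition 10%.

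**Step 1: reproduce 338 at 17% vs 8.3%.**
- P1(1 − P1) + P2(1 − P2) = 0.1411 + 0.0761 = 0.2172, and (P1 − P2)² = 0.087² = 0.007569.
- Unpooled variance: n = (1.960 + 0.8416)² × 0.2172 / 0.007569 = 225.2. Then 225.2 × 1.5 = **337.9**, which is the printed 338.
- Formula as printed: mean p = 0.1265, so 2pq = 0.2210. n = (1.960 × √0.2210 + 0.8416 × √0.2172)² / 0.007569 = 228.0. Then 228.0 × 1.5 = **342.0**, close to 338.

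Neither product contains an attrition factor.

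**Step 2: add the stated 10% attrition.**

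| Variant, 17% vs 8.3% | n × 1.5 | × 1.1 | ÷ 0.9 |
|---|---|---|---|
| Unpooled | 337.9 | 371.7 | 375.4 |
| Pooled, as printed | 342.0 | 376.2 | 380.0 |

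With exact 4/24 vs 2/24 the gap widens: the printed formula gives 246.1 × 1.5 = 369.1 before attrition and 410.1 after dividing by 0.9.

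**Step 3: what the formula's n counts.** The variance of a difference between two proportions with n in each group is [P1(1 − P1) + P2(1 − P2)]/n. The printed expression solves this for n, so n is the number per arm. The total is 2n. Before attrition that is 2 × 337.9 = 676 (unpooled) or 2 × 342.0 = 684 (pooled). After dividing by 0.9 it is 751 or 760. With exact 4/24 vs 2/24 it is 811 or 820.

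**Step 4: power at the planned size.** I inverted the printed formula, with each arm's number divided by 1.5:

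power = Φ{[(P1 − P2)√m − 1.960√(2pq)] / √(P1(1 − P1) + P2(1 − P2))}, where m is the effective number per arm.

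| Women per arm | m | 17% vs 8.3% | 4/24 vs 2/24 |
|---|---|---|---|
| 170, no loss | 113.3 | 50.4% | 47.5% |
| 153 (10% lost) | 102.0 | 46.3% | 43.6% |
| 340, no loss | 226.7 | 79.8% | 76.7% |
| 306 (10% lost) | 204.0 | 75.5% | 72.2% |

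The last two rows show that 338 to 340 delivers about 80% power only as a per-arm number, at the rounded rates and with nobody lost.

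**The case against.** Three points can be made on the other side.

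First, some calculations do land near 338 with attrition included. A one-sided, continuity-corrected n of 201.8 gives 201.8 × 1.5 / 0.9 = 336. A one-sample version, or P2 rounded down to 8%, also comes close (17% vs 8% gives about 343 to 351 with the two-sided pooled and unpooled formulas). So it cannot be said that 338 is unobtainable with attrition under any method. Each of these, however, departs from what the section prints: Z at 1 − α/2, two samples, no continuity correction, 8.3%.

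Second, the exact match of 337.9 uses unpooled variance and the rounded rates, whereas the printed pooled formula gives 342.0. That is true, but both reach 338 on the design effect alone, and the exact fractions give still larger numbers.

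Third, a reader might infer that the trial has 80% power with full retention, and that 10% loss would take it to about 75%. The document does not support this. Those figures describe about 340 women per arm, whereas the article allots about 170. At that size power starts near 50%, and 10% loss costs about four further points. For the same reason, 372 to 380 should not be read as an adequate total. The per-arm result used as a total is the larger of the two faults. Doubling 338 to 676 would repair that fault and still leave no attrition allowance.

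**Conclusion.** The point stands. Under the printed formula and rates, 338 carries the design effect but not the 10% attrition. On the article's own reading of n, including attrition would give 372 to 380. This omission persists whether 338 is read as a total or as a per-arm number.

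Its effect on power has to be judged at the planned allocation: about 50% with no loss and 46% after 10% loss at 17% vs 8.3%, or about 47% and 44% at 4/24 vs 2/24. The stated 80% is not delivered in any of these cases.

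These figures take the article's rates, two-sided 5% level, design effect of 1.5 and 10% loss as given. They describe the simple comparison of two proportions on which the section bases its size. They do not describe the difference-in-differences analysis, whose power cannot be computed from the inputs given.

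**What to change.** In the sample size section, either state that 338 contains no allowance for attrition or remove the 10% attrition rate from its listed inputs. Neither change is enough alone, because each would leave a total of 338 credited with 80% power. So also replace the 80% claim with the power expected at 170 per arm after 10% loss, about 44 to 46%, and describe the formula's result as per arm.

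Any recalculated size should take n per arm, multiply by 1.5, then divide by 0.9. That gives about 751 to 760 women in total at 17% vs 8.3%, or 811 to 820 at 4/24 vs 2/24.

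The correction restates figures and does not require extra enrolment, so it can be made while the study is running. Its cost is a less favourable stated power.
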